## Abstract

**Background:**

Even without weight loss, adults with obesity can greatly benefit from regular physical activity. The Physical Activity Self-efficacy (PAS) intervention is an online behavioral intervention newly developed to promote physical activity in adults with obesity by providing capability-enhancing learning opportunities. The objective of this manuscript is to describe the protocol for a feasibility study designed to investigate the feasibility and acceptability of implementing the PAS online intervention for adults with obesity recruited from a local weight management center in the United States of America (USA).

**Methods:**

The study design is a prospective, double-blind, parallel-group individual randomized pilot trial. Thirty participants will be randomly assigned to the PAS group or usual care group to achieve a 1:1 group assignment. Recruitment of participants is scheduled to begin on 1 March 2024 at a local weight management center within a private healthcare system in the USA. There are six eligibility criteria for participation in this study (e.g., a body mass index ≥ 25.00 kg/m^2^). Eligibility verification and data collection will be conducted online. Three waves of data collection will take up to 14 weeks depending on participants’ progress in the study. The primary feasibility outcomes in the study will be: (a) participation rate, (b) engagement behavior, and (c) a preliminary effect size estimate for the effect of the PAS intervention on physical activity. Instruments designed to measure demographic information, anthropometric characteristics, self-efficacy, and acceptability will be included in the survey battery. A research-grade accelerometer will be used to measure free-living physical activity objectively. Data will be analyzed using descriptive statistics and inferential statistical models under an intention-to-treat approach.

**Discussion:**

Results are intended to inform the preparation of a future definitive randomized controlled trial.

**Trial registration:**

ClinicalTrials.gov, NCT05935111, registered 7 July 2023.

**Supplementary Information:**

The online version contains supplementary material available at 10.1186/s40814-024-01468-6.

## Background

The relationship between physical activity (PA) and health is not well understood by adults with obesity, not even by some health professionals. There is a misguided understanding that PA in adults with obesity should result in weight loss to obtain health benefits [1, 2]. However, there is strong evidence that, even without weight loss, adults with obesity can greatly benefit from regular PA for multiple reasons (e.g., relative reduction in incidence or progression of a chronic disease; improvements in insulin sensitivity, blood pressure, and body composition; attenuated weight gain; etc.) [3, 4]. In addition, previous meta-analyses have reported that promoting physical activity may help improve the mental health of adults with obesity [5, 6]. Having PA mainly for weight loss is problematic because adults with obesity may feel disheartened and lose motivation for PA if weight loss is not achieved at a satisfactory rate, or not at all. As expected, there is persistent evidence that most adults with obesity do not meet public health guidelines for PA [7, 8], for example, 150 min per week of moderate PA [3, 9, 10].

Based on extensive literature review [2, 11–26], we propose to develop and test a new online behavioral intervention, named the Physical Activity Self-efficacy (PAS) intervention. The PAS intervention is an online behavioral intervention specifically designed to promote PA in adults with obesity by providing capability-enhancing learning opportunities. The PAS intervention is: (a) population-tailored (i.e., adults with obesity), (b) aimed to promote multi-dimensional PA (i.e., work-, transport-, domestic-, leisure-related PA), (c) theory-based (i.e., self-efficacy theory), (d) scalable and sustainable (i.e., online delivery), (e) implemented with device-based PA assessments (i.e., an accelerometer), and (f) collaborated with an external community partner (i.e., a local weight management center), to promote PA in adults with obesity. A recent systematic review showed that the majority of research- or commercial-grade online interventions did not address some unique barriers to PA from adults with obesity but only added typical PA advice into diet-focused interventions [27]. In the absence of the proposed intervention, promoting PA in adults with obesity will likely remain difficult in reality.

The PAS intervention builds off the Fun For Wellness (FFW) intervention [28–31]. Compared to FFW, the PAS intervention is more tailored for adults with obesity (i.e., at-risk subgroup of adults) and specifically designed to promote PA (i.e., not well-being) to achieve greater behavior change for their PA. Self-efficacy is specified as a mediating psychological variable in the conceptual model for the promotion of PA (see Fig. 1). Self-efficacy refers to domain-specific beliefs about their ability to execute differing levels of performance given situational demands [32–34]. There is a rich literature on the importance of targeting self-efficacy as a modifiable mediating variable in PA interventions [35–37]. The PAS intervention consists of 6 intervention components. Across the intervention components, there is a total of 30 introductory or post-introductory challenges in the PAS intervention. Precise reporting of the PAS intervention (e.g., how PAS builds off FFW) is provided in Appendix A, consistent with relevant recommendations [38, 39].

**Fig. 1 Fig1:**
[figure not shown]
The conceptual model of the physical activity self-efficacy intervention

The objective of this manuscript is to describe the protocol for a feasibility study designed to investigate the feasibility and acceptability of implementing the PAS online intervention for adults with obesity recruited from a local weight management center in the United States of America (USA). Three specific aims will be investigated. 

### Aim 1

To determine the feasibility of implementing the PAS intervention (e.g., participation rate) for adults with obesity.

### Aim 2

To determine the acceptability of implementing the PAS intervention (e.g., engagement behavior) for adults with obesity.

### Aim 3

To provide a preliminary effect size estimate for each direct effect depicted in the conceptual model (see Fig. 1) for the PAS intervention (e.g., PAS  →  PA).

## Methods

This protocol was written based on the Standard Protocol Items: Recommendations for Interventional Trials (SPIRIT) [40, 41]. A SPIRIT flow diagram is provided in Table 1. A populated SPIRIT checklist is provided in Appendix B. The trial was registered at ClinicalTrials.gov, identifier: NCT05935111, registered 7 July 2023.

**Table 1 Tab1:**
[figure not shown]
The SPIRIT flow diagram for the physical activity self-efficacy intervention feasibility study

*PAS* Physical Activity Self-efficacy, *UC* Usual Care

### Ethical approval

All procedures in this study involving human participants will be in accordance with the ethical standards of the institutional and national research committee. The institutional review board at Ascension provided necessary permission to conduct this study on 14 July 2023, RNY20230009. The procedures for confidentiality are provided in Appendix C.

### Study design

The study design is a prospective, double-blind, parallel-group individual randomized pilot trial. Recruitment of participants is scheduled to begin in March 2024 at a local weight management center within a private healthcare system in the USA. Eligibility verification and data collection will be conducted online. Three waves of data collection will take up to 14 weeks depending on participants’ progress in the study. Figure 2 provides a flow chart for recruitment of participants throughout data collection.

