### Randomization

Thirty participants will be randomly assigned to the PAS group or the Usual Care (UC) group to achieve a 1:1 group assignment. The randomization will be performed by the PAS intervention website (i.e., computer-generated random numbers). Neither participants nor the research staff will know which group a participant will be assigned into.

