### UC group

The UC participants will proceed through the weight management program provided by the center. The login credentials for UC participants will provide access to a secure website to complete data collection at wave 1 (W1), wave 2 (W2), and wave 3 (W3). The UC participants will have the opportunity to receive up to $90 worth of Amazon electronic gift cards. Specifically, UC participants will receive: (a) $5 for completing the W1 survey battery, (b) $35 for completing the W1 PA monitoring for 7 days, (c) $5 for completing the W2 survey battery, (d) $5 for completing the W3 survey battery, and (e) $40 for completing the W3 PA monitoring for 7 days. The UC participants will be given 4 weeks of 24-h access to the PAS intervention immediately after data collection for the study is closed.

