### PAS group

The PAS participants will proceed through the weight management program and will be given 4 weeks of 24-h access to the PAS intervention during data collection for this study. The login credentials for PAS participants will provide access to both the PAS intervention and to a secure website to complete data collection at W1, W2, and W3. The PAS participants will have the opportunity to receive up to $110 worth of Amazon electronic gift cards, which is the sum of the same gift card opportunities from the UC group (i.e., $90) and an additional $20 for completing at least 24 post-introductory challenges in the PAS intervention at W2.

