### ActiGraph wGT3X-BT

The ActiGraph wGT3X-BT (Pensacola, FL, USA) is a tri-axial research-grade accelerometer that will be used to measure PA objectively. ActiGraph devices have been used extensively as a reference device to measure free-living PA in adults [57]. Monitors will be initialized to collect raw acceleration data at 30 Hz using ActiLife software (v6.13.4). After download, data will be reintegrated to 60-s epochs. Non-wear time will be defined as ≥ 90 continuous minutes of zero counts, with allowance for 2 min of acceleration which are preceded and followed by at least 30 min of continuous zeros [58]. Usable data will be defined as follows: (a) a monitor is worn for at least 4 days including one weekend day with at least 10 h of valid wear time per day, (b) there is no evidence of monitor error, and (c) there is no issue from data compared to a log sheet. Unusable data will be treated as missing data. Average minutes per day of MVPA will be calculated based on established cut points (e.g., > 1952 counts per minute) [59].

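### The trial is labelled double-blind, but participants can tell their arm once PAS access opens after W1, and whether staff stay blinded is unclear

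*Protocol article*

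**What the plan says.** The Abstract and the Study design section both call the trial double-blind; the latter reads: "The study design is a prospective, double-blind, parallel-group individual randomized pilot trial". The Randomization section states: "The randomization will be performed by the PAS intervention website", and adds: "Neither participants nor the research staff will know which group a participant will be assigned into".

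The two arms are described as follows.

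- For usual care, the UC group section says: "The login credentials for UC participants will provide access to a secure website to complete data collection", and "The UC participants will be given 4 weeks of 24-h access to the PAS intervention immediately after data collection for the study is closed".
- For the intervention arm, the PAS group section says: "The login credentials for PAS participants will provide access to both the PAS intervention and to a secure website to complete data collection". This arm can also earn a further $20 for completing 24 or more of the post-introductory challenges.

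The Study timeline section opens PAS access after W1. W1 comprises both the first survey battery and the first week of activity monitoring. There is no activity monitoring at W2.

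Under PA monitoring, research staff meet each participant at the center to hand over the monitor package. Under ActiGraph wGT3X-BT, one of the conditions for usable data is that "there is no issue from data compared to a log sheet".

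**The concern.** A double-blind label tells readers that participants' knowledge of their allocation cannot explain a difference between the arms. Here the comparator is usual care and the intervention is a website that participants either have or do not have, so the label promises a protection that the design does not give them.

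The protection matters most for self-report. The two self-efficacy scales completed by both arms and the IPAQ are answered by the participants themselves. One arm has just used a program built to raise self-efficacy. Under Aim 3, effects of assignment at W2 or W3 are read against a red bound of below 0.00 and a green bound of 0.20 or more. If readers believe the trial was double-blind, they will discount response bias as an explanation for a green result, and these results are meant to inform a definitive trial.

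A second question is whether staff stay blinded. The usability decision determines which accelerometer values exist for the Aim 3 primary estimate. Where accelerometer data are counted, it also enters the Aim 1 primary outcome, the participation rate.

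**Working it through.** This is mainly a comparison of sections, with a little arithmetic.

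**1. Can participants tell their arm?**

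| Feature | PAS | UC | Section |
|---|---|---|---|
| Intervention open during data collection | yes, 4 weeks | no, only afterwards | PAS group; UC group |
| Maximum gift cards | 90 + 20 = $110 | 5 + 35 + 5 + 5 + 40 = $90 | PAS group; UC group |
| Self-efficacy-to-engage scale at W2 | yes | no | Self-efficacy to engage |
| Intervention acceptability questionnaire at W2 | yes | no | Acceptability of the PAS intervention |
| Sham or attention-control site | none described | none described | n/a |

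Both gift-card totals agree with the protocol. Each of the first four rows separates the arms in a way that participants can see. From the opening of access after W1, they can tell which arm they are in.

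**2. Which measurements does this touch?**

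- W1 measures precede PAS access, so access itself does not unblind them.
- At W2 there is no activity monitoring, so the outcome contrasts between the arms rest on self-report, chiefly the two self-efficacy scales.
- At W3 the self-efficacy scales are repeated and the IPAQ follows the wear week. All are self-reported after the arm is known.
- The Aim 3 primary outcome is accelerometer MVPA, which self-report cannot shift directly. Knowing the arm can still change behaviour or wear.
- The Aim 2 primary outcome is logged by the website in the PAS arm only, so it is not a between-arm contrast.

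**3. Response bias and the 0.20 bound.** If the true standardized effect is zero and reporting in the PAS arm shifts by b standard deviations, the expected estimate is b. Any b of at least 0 but below 0.20 leaves the average result yellow; b of 0.20 or more makes it green. The documents give no value for b, so this shows what the bound tolerates and is not an estimate of bias.

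**4. Staff.** The sentence on who will know the assignment is in the future tense and follows the description of computer randomization. It can mean that the coming allocation is concealed, or that staff remain blinded throughout. The website randomizes and delivers the intervention, so staff need not learn the arm. They do meet participants in person to deliver monitors, including for W3, when participants can know it.

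**5. Usability.** Fixed rules cover wear days, the weekend day, daily hours and non-wear. The log-sheet comparison, and perhaps the check for monitor error, needs judgement. Participation rate is defined over all consented patients, with a target of 30:

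- one call: 1/30 = 3.3 points
- two calls: 2/30 = 6.7 points

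The bounds of 50% and 70% correspond to 0.50 × 30 = 15 and 0.70 × 30 = 21 participants. One call can therefore change the colour only at an edge: 20/30 = 66.7% is yellow and 21/30 = 70% is green. The W2 rate is unaffected, because no monitor is worn then.

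**The case against.** The strongest reply is that the primary outcomes are largely insulated. Accelerometer MVPA is device-measured and engagement is logged automatically, while the self-efficacy contrasts are secondary. Self-efficacy is also the intended mediator, so a rise after the intervention is not bias by default. The study is a 30-person pilot, not sized for power. All of this stands and limits the consequence. It does not make the label true for participants.

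A reader might be tempted by four stronger conclusions that the documents do not support.

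- *Accelerometer usability has no blinding protection.* The Randomization section may assert continuing staff blinding, and most of the usability definition is rule-based. Loss of staff blinding at monitor delivery is possible but is not shown.
- *The arm is visible before baseline is complete.* PAS access opens after W1. The timing of randomization relative to W1 is not given, and nothing says that the logins look different during W1.
- *One or two usability calls move the participation rate by 7 to 13 points.* That uses 15 per arm (1/15 and 2/15). The protocol's rate is over all consented patients.
- *The trial should be called open-label.* That would discard staff blinding that the protocol may intend.

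The appendices, Table 1 and the figures are not shown and may say more about staff. They could not undo the arm descriptions for participants. An article may also leave masked scoring to a fuller document, so its absence is not the fault here. The fault is a blinding claim that the article's own text contradicts for participants and leaves ambiguous for staff.

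**Conclusion.** The concern holds for participants: the double-blind label is wrong from the opening of PAS access after W1. This rests only on the arm descriptions, with no sham site described.

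The W2 and W3 self-efficacy contrasts, and any W3 IPAQ contrast, are unblinded self-report. A green result on them cannot by itself separate a real change from a response shift. The size of such a shift is unknown from the documents. The device-measured primary estimate is less exposed, though not immune through behaviour and wear.

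Staff blinding is unclear, not shown to be absent. The exposure through judged usability calls is 3.3 to 6.7 points of the W1 or W3 participation rate for one or two calls. This assumes that 30 participants consent and that accelerometer data count toward usable data at that wave.

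**What to change.** 1. Remove the double-blind label from the Abstract and the Study design section, and state that participants are not blinded once PAS access opens.
2. In the Randomization section, reword the sentence on who knows the assignment as allocation concealment if that is what is meant. Otherwise, state which roles remain blinded and until when.
3. Have the log-sheet comparison and the monitor-error check made on files whose arm codes are masked.
4. When applying the traffic-light thresholds, report the self-efficacy and IPAQ effects as unblinded self-report.

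The cost is wording and masked file IDs. The sample size, visits and measurements do not change.

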**Fig. 2 Fig2:**
[figure not shown]
Flow chart for the implementation of the physical activity self-efficacy intervention

### Recruitment

Thirty participants will be recruited in this study. Patients who are enrolling in the weight management program provided by the center will be potential participants in the study (e.g., ~ 70 potential participants). They will be asked to consider their participation in this study by a research staff member who is affiliated with the center via in-person communication or remote communication. The research staff will provide only those interested in the study (e.g., ≤ 70 potential participants) with login information to the secure recruitment page on the PAS website which can then be accessed via their own device (e.g., smartphone). The PAS website will automatically stop recruitment once 30 participants provide their remote consent forms. We expect that the recruitment may take about one month.

### Eligibility and informed consent

There are six eligibility criteria that will be evaluated via self-report: (a) being between 18 and 64 years old, (b) a Body Mass Index (BMI) ≥ 25.00 kg/m^2^, (c) the ability to access the online intervention, (d) the absence of simultaneous enrollment in another intervention to promote PA (not counting the weight management program), (e) a willingness to comply with instructions for PA monitoring, and (f) a willingness to respond to study-related contacts. Detailed information and justifications for the criteria are provided in Appendix D. Those who meet all the eligibility criteria will be presented with the informed consent form to read and sign electronically.

### Sample size

The sample size (i.e., 30 participants) is based on the primary feasibility outcomes (see the feasibility outcome section for detailed information), the budgetary constraints, and the range of sample sizes observed in pilot and feasibility trials. Thirty participants may provide some data to use descriptive statistics for the primary feasibility outcomes (i.e., participation rate in Aim 1, engagement behavior in Aim 2). If the recruitment rate is 50% in this study, the targeted sample size can be used because the center usually has approximately 70 patients enrolled in their program. Budgetary constraints preclude enrollment of more than 30 participants in this study. Also, the targeted number of participants may provide some data about the preliminary effect size estimate for the direct effect of PAS to PA. The sample size in a feasibility study is not based on a sample size determination for a desired level of statistical power [42–44]. The target sample size in this study fits within the range of sample sizes often observed in pilot and feasibility trials [45].

### Randomization

Thirty participants will be randomly assigned to the PAS group or the Usual Care (UC) group to achieve a 1:1 group assignment. The randomization will be performed by the PAS intervention website (i.e., computer-generated random numbers). Neither participants nor the research staff will know which group a participant will be assigned into.

### UC group

The UC participants will proceed through the weight management program provided by the center. The login credentials for UC participants will provide access to a secure website to complete data collection at wave 1 (W1), wave 2 (W2), and wave 3 (W3). The UC participants will have the opportunity to receive up to $90 worth of Amazon electronic gift cards. Specifically, UC participants will receive: (a) $5 for completing the W1 survey battery, (b) $35 for completing the W1 PA monitoring for 7 days, (c) $5 for completing the W2 survey battery, (d) $5 for completing the W3 survey battery, and (e) $40 for completing the W3 PA monitoring for 7 days. The UC participants will be given 4 weeks of 24-h access to the PAS intervention immediately after data collection for the study is closed.

### PAS group

The PAS participants will proceed through the weight management program and will be given 4 weeks of 24-h access to the PAS intervention during data collection for this study. The login credentials for PAS participants will provide access to both the PAS intervention and to a secure website to complete data collection at W1, W2, and W3. The PAS participants will have the opportunity to receive up to $110 worth of Amazon electronic gift cards, which is the sum of the same gift card opportunities from the UC group (i.e., $90) and an additional $20 for completing at least 24 post-introductory challenges in the PAS intervention at W2.

